### Statistical consideration

#### Sample size determination

No randomized trials have been performed of elective PCI versus no PCI in patients undergoing TAVI. In a recent nonrandomized registry, Masson *et al*. reported a 1-year mortality of 20% in 15 patients who underwent PCI prior to TAVI - similar to those who did not at 22.1% [4] - despite the presence of existing coronary disease having been shown to increase mortality in patients undergoing TAVI from 18.4 to 35.7% [5].

With the postulation that improved coronary perfusion may protect against some of the ischemic/hypotensive procedural complications of the TAVI procedure, an improvement in rate of mortality seems likely. PCI may lead to restenosis of the stent, requiring rehospitalization in 5% of patients over 12 months. The rate of rehospitalization with stable angina, acute coronary syndrome or ischemia-related heart failure requiring treatment, including possible PCI, is thought to be in the region of 15% in all patients with CAD. The feasibility assumptions for 12-month mortality are 30% in the control (TAVI only) arm and 20% in the test (TAVI + PCI) arm, with similar rates of hospitalization at 15% in both. Based on the above assumptions, we performed sample size simulations and the simulated results show that with a non-inferiority margin of 7.5% and a loss to follow up of 5%, the sample size of 310 patients will have at least 88.8% power to demonstrate non-inferiority of TAVR following PCI compared with TAVR without PIC in the primary endpoint.

### Statistical analysis

For the primary endpoint analysis, cumulative event rate will be calculated using the Kaplan-Meier estimates, and the Greenwood standard errors for these estimates. A 95% one-sided upper confidence limit will be computed for the difference in the primary composite outcome of mortality of rehospitalization at 12 months between arms (Test - Control). The Test arm (PCI) will be judged not inferior to the Control arm (no PCI) if the upper confidence limit is less than 7.5% - the predetermined non-inferiority margin. This was chosen based upon expert opinion and precedent (PARTNER cohort A [29]). In addition to formal analysis of non-inferiority endpoints, the Kaplan-Meier curves will be presented and compared by log rank test by treatment group and hazard ratio and its 95% confidence interval will be calculated using Cox regression model. Also, the combination of the all cause mortality and time to first recurrent hospitalization will be analyzed using the unmatched win ratio approach [35].

For secondary time-to-event outcomes, event rates at 30 and 365 days will be calculated using the Kaplan-Meier method and compared by log rank test. Their hazard ratios will be estimated using Cox regression model. Outcomes with repeated measurements will be analyzed using generalized linear mixed models. Continuous variables will be summarized using number of observations, median (interquartile range) or mean (SD) depending on variable distributions, whereas categorical variables will be summarized by the number and percentage of events. Chi-square tests and Mann-Whitney methods will also be used for comparative purposes. All analyses will be performed both on intention to treat and as treated populations.

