**Table 2 Tab2:** **Endpoint definitions**

End-point	Definition
**Mortality**	All-cause death
**Cardiovascular mortality**	All deaths unless otherwise clearly documented to be related to another cause (for example, trauma, cancer, suicide *etcetera*)
**Myocardial infarction (MI)**	Peri-procedural MI related to TAVI (≤72 h after the TAVI)
	Spontaneous MI (>72 h after TAVI)
	MI related to PCI (type 4a)
	MI related to PCI due to stent thrombosis (type 4b)
**Cerebrovascular event**	Stroke
	Transient ischemic attack
**Bleeding complication**	Life-threatening or disabling
	Major
	Minor
**Access site complication**	Major
	Minor
**Acute kidney injury** As per AKIN classification in VARC2 [34]	Stage 1
	Stage 2
	Stage 3
**Major adverse cardiac and cerebrovascular events (MACCE)**	Combined cardiovascular mortality, MI, stroke and further revascularization

TAVI, transcatheter aortic valve implantation; PCI, percutaneous coronary intervention, AKIN, acute kidney injury network; VARC2, Valve Academic Research Consortium second guidelines [34].

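### Kaplan-Meier 365-day rates for non-fatal secondary outcomes censor deaths and so overstate absolute risk, by about 11% and 18-19% relative at the plan's assumed 20% and 30% mortality

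*Protocol article*

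**What the plan says.** The Statistical analysis section of the protocol article sets the method for all secondary time-to-event outcomes together: "For secondary time-to-event outcomes, event rates at 30 and 365 days will be calculated using the Kaplan-Meier method and compared by log rank test". The effect measure follows: "Their hazard ratios will be estimated using Cox regression model". No exception is made for outcomes that death can prevent, and no competing-risk method is mentioned.

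The Secondary endpoints section lists MI, stroke and heart-failure hospitalization, each at 30 days and 12 months, and repeat revascularization. None of these contains death. Table 2 defines MACCE as "Combined cardiovascular mortality, MI, stroke and further revascularization", so it counts cardiovascular but not other deaths.

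The Sample size determination section gives the expected mortality: "The feasibility assumptions for 12-month mortality are 30% in the control (TAVI only) arm and 20% in the test (TAVI + PCI) arm". It continues: "with similar rates of hospitalization at 15% in both".

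**The concern.** One minus Kaplan-Meier for a non-fatal event, with deaths censored, estimates the risk in a hypothetical population in which nobody dies first. That is not the proportion of these patients who have a stroke, an MI or an admission within a year. The gap is negligible where few patients die. Here the plan expects one patient in five, or nearly one in three, to die within 12 months.

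What is at stake is the absolute 365-day rates. Readers will use them to weigh an extra procedure before TAVI, and they would be too high. If mortality differs between arms as planned, they would be too high by a different factor in each arm. Because the article names the method, this is a choice that it fixes, and not detail left to a longer document.

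**Working it through.** **Inputs**
- 12-month mortality: 20% test, 30% control (Sample size determination).
- 12-month hospitalization: 15% in both arms (same section). This is the plan's assumption for a component of the primary endpoint, used here as an example of a non-fatal event rate.
- Assumed, because the article does not state them: 1:1 allocation and, for the base case, constant hazards.

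**Checking that the inputs are read as the plan used them.** The article gives no figure for Kaplan-Meier bias. Its one computed figure is power: "the sample size of 310 patients will have at least 88.8% power".
- Death and hospitalization combined as independent risks: control 1 − 0.70 × 0.85 = 40.5%; test 1 − 0.80 × 0.85 = 32.0%.
- 310 patients less 5% loss is about 147 per arm.
- Standard error = √[(0.405 × 0.595 + 0.320 × 0.680)/147] = 0.0559.
- With the margin of 7.5% and a one-sided 95% limit: 0.160/0.0559 − 1.645 = 1.22, so power is 88.9%.

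The stated power is reproduced with death and hospitalization treated as two separate risks.

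**365-day rates, constant hazards.** Let e = −ln(1 − event risk) and d = −ln(1 − mortality). Kaplan-Meier with deaths censored estimates 1 − exp(−e). The proportion who actually have the event is the cumulative incidence, e/(e + d) × [1 − exp(−(e + d))].

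For a Kaplan-Meier rate of 15%, e = 0.1625.
- Test: d = −ln(0.80) = 0.2231. Cumulative incidence = 0.1625/0.3857 × 0.320 = 13.5%. Ratio 0.15/0.1348 = 1.11, an excess of 1.5 points.
- Control: d = −ln(0.70) = 0.3567. Cumulative incidence = 0.1625/0.5192 × 0.405 = 12.7%. Ratio 0.15/0.1268 = 1.18, an excess of 2.3 points.

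For event risks from 2% to 20%, the overstatement is 11.1-11.5% at 20% mortality and 18.0-18.8% at 30%.

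**Sensitivity to timing** (Weibull cumulative hazards, Kaplan-Meier rate 15%):

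| Event shape | Death shape | Overstatement at 20% mortality | Overstatement at 30% mortality |
|---|---|---|---|
| equal shapes (constant ratio) | same | 11% | 18% |
| 0.3 (events early) | 1 | 5% | 8% |
| 1 | 0.3 (deaths early) | 18% | 31% |
| 1.5 (events late) | 0.3 (deaths early) | 20% | 34% |

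The direction is upward in every case.

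**30-day rates.** With constant hazards and t = 30/365, Kaplan-Meier gives 1.327%. The cumulative incidence is 1.315% (test) and 1.308% (control), so the ratios are 1.009 and 1.015. This figure needs hazards that are constant in time, not merely in constant ratio. If both hazards were strongly front-loaded (shape 0.3), the 30-day overstatement would be about 5% and 9%.

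**Dependence on the mortality gap.** The Sample size determination section also quotes registry mortality of 20% with PCI and 22.1% without. At 22.1%, d = 0.2497 and the cumulative incidence is 0.1625/0.4123 × 0.3379 = 13.3%, a ratio of 1.13. The two arms would then be overstated by 11% and 13%, nearly the same.

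**The case against.** The strongest objection concerns the comparison between arms. A reader might infer that the planned comparisons of stroke, MI and admissions are distorted by the mortality difference. The article does not support that. It compares arms by log-rank test and Cox hazard ratio, and both remain valid for the cause-specific hazard when deaths are censored. In the worked example the event hazard is equal in both arms, so finding no difference is the correct cause-specific answer. The 0.8-point difference in cumulative incidence (13.5% − 12.7%) arises because more control patients die before they can be admitted. For the same reason Gray's test would not correct an error; it answers a different question. This objection stands, and it limits the point to the absolute rates.

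Other points also stand:
- The 11-19% range cannot be quoted without its conditions. It holds at 365 days and for hazards in constant ratio. Peri-procedural MI, for example, may well come early, which points to the lower end of the sensitivity range.
- The range does not carry over to MACCE. Only non-cardiovascular death competes there, and the Primary endpoint section treats deaths as cardiovascular unless documented otherwise. The effect is smaller, and the article gives no figure from which to compute it.
- The inequality between arms rests on the 30% versus 20% assumption.
- In absolute terms the distortion is small. For a 5% outcome, Kaplan-Meier overstates by 0.8 points (control) and 0.5 points (test), a gap of about 0.3 points. With about 155 per arm, the standard error of a difference is √(2 × 0.05 × 0.95/155) = 2.5 points, and 4.1 points for a 15% outcome. The gap between arms is thus about 0.1-0.2 standard errors.

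The article also plans numbers and percentages for categorical variables. If these are given for the same outcomes, they would lie close to the cumulative incidence, but the article does not say that they will be.

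None of this makes the Kaplan-Meier figure a correct 365-day event rate for an outcome that death prevents.

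**Conclusion.** The point holds for the absolute 365-day rates of MI, stroke, repeat revascularization and heart-failure hospitalization. At the plan's assumed 20% and 30% mortality they are overstated by about 11% and 18-19% relative if event and death hazards keep a constant ratio, by roughly 5-8% if events come early, and by 18-31% or more if deaths come early. At 30 days, with constant hazards, the overstatement is about 1-1.5%. The bias differs between arms only to the extent that mortality does. MACCE is affected through documented non-cardiovascular death alone.

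A reader might go further and infer that the primary result is compromised. It is not: the primary composite and all-cause mortality both count every death, so Kaplan-Meier is appropriate for them, and no decision rule or power figure depends on the secondary rates. This should be corrected, as a fault in how secondary results are estimated and reported.

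**What to change.** For each secondary time-to-event outcome that does not include all-cause death, report Aalen-Johansen cumulative incidence at 30 and 365 days, with a confidence interval for the difference between arms. The competing event is death, or non-cardiovascular death for MACCE. Keep the log-rank test and Cox hazard ratio, and label them cause-specific. Gray's test is optional. Keep Kaplan-Meier for all-cause mortality and the primary composite.

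The cost is a few lines of text and a little more analysis with standard software. The date and nature of each death are already to be recorded, so no new data are needed, and neither the sample size nor the primary analysis changes. The one drawback is that the rates will be slightly lower than Kaplan-Meier figures in older reports; a footnote can say so.

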### Primary endpoint

The primary endpoint is a composite of mortality and rehospitalization at 12 months since randomization. Mortality is defined as death due to any cause, the exact nature and date of which will be recorded. All deaths will be considered cardiovascular-related unless there is documentation to the contrary.

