### Randomization

Randomization will take place once the patient has provided written, informed consent. This will be performed via an online portal. Randomization of the treatment assignment is based on the block method using randomly varying block sizes and will be stratified by center. Once the patient is randomized s/he will be monitored for the duration of the follow-up irrespective of subsequent clinical management. The intended timeframe for PCI should be stated at randomization. After PCI the patient should receive dual anti-platelet therapy for 30 days - one of which can then stop if the patient receives a bare-metal stent (BMS). All PCI patients should undergo TAVI within the 2 weeks after this 30-day post-PCI time point. Any clinical events which occur in the test arm during this period will be attributed to the percutaneous revascularization on an intention-to-treat-basis. The flow diagram in Figure 1 illustrates the recruitment and study process.

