#### Data collection and monitoring

Data will be collected at baseline from enrolled patients including demographics, past medical history, previous cardiac investigations and current medication. Patients will undergo transthoracic ± transesophageal echocardiography at baseline, post-procedure, 1 month and 12 months. Twelve-lead electrocardiograms will be obtained at the same time points, with additional traces in the test arm pre- and post-PCI and in either arm after any clinical event thought to represent myocardial infarction and before/after any subsequent revascularization procedure. In addition to routine blood tests, a full blood count will be taken pre- and post-PCI.

Prospective monitoring of adverse and clinical events starts at randomization and continues until 12 months. Patients should be followed up to hospital discharge following PCI. All MACCE will be documented by the research coordinator using the clinical event data form. The same applies for the TAVI procedure. Patients will be followed up at 30 days and 12 months for anginal burden using the Seattle Angina Questionnaire and other end-points. Mortality data will be obtained from the Office of National Statistics in England and Wales, the General Register Office in Scotland and from the appropriate authority in other countries.

All MACCE and other serious adverse events will be recorded in the electronic Case Record Form and reported to the coordinating center within 3 working days of first identification. On receipt of notification of any trial adverse or clinical event, the coordinating center will request additional details, specific to the nature of the event. These episodes will be carefully monitored by the trial coordinator and will form part of the information provided at regular intervals to the Clinical Events and Data Monitoring Committees. The study site will also notify their ethics committee and institutional clinical risk management team according to their local policy. The Clinical Events Committee will be blinded to treatment and will consider each MACCE or adverse event reported and ratify occurrence of an endpoint according to the study definitions (according to a majority).

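### Secondary mortality is counted from TAVI, so it drops test-arm deaths from PCI and the 30 to 44 day wait; the other 30-day event outcomes have no stated origin, and neither candidate compares the full strategies

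*Protocol article*

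**What the plan says.** **Schedule.** Under Randomization, the article says of the test arm: "All PCI patients should undergo TAVI within the 2 weeks after this 30-day post-PCI time point". The delay from randomization to PCI is not fixed: "The intended timeframe for PCI should be stated at randomization". No TAVI timing is given for the control arm. On the interval between PCI and TAVI, the same section says: "Any clinical events which occur in the test arm during this period will be attributed to the percutaneous revascularization on an intention-to-treat-basis".

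**Time origins.**
- Primary endpoint: "The primary endpoint is a composite of mortality and rehospitalization at 12 months since randomization".
- Secondary endpoints, item (i): mortality at 30 days and 12 months is counted from TAVI.
- Secondary endpoints, items (ii), (iii), (iv) and (vi): MACCE, MI, stroke and heart-failure hospitalization are given at 30 days and 12 months, with no origin.

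**Analysis.** For secondary time-to-event outcomes, "event rates at 30 and 365 days will be calculated using the Kaplan-Meier method and compared by log rank test". The Statistical analysis section closes by committing every analysis to both an intention-to-treat and an as-treated population.

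**Data collection.** "Prospective monitoring of adverse and clinical events starts at randomization and continues until 12 months". For visits: "Patients will be followed up at 30 days and 12 months for anginal burden using the Seattle Angina Questionnaire and other end-points" and "Patients will undergo transthoracic ± transesophageal echocardiography at baseline, post-procedure, 1 month and 12 months". ECGs follow the echo time points.

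**The concern.** TAVI is the common procedure, and in the test arm it comes at least 30 days after the randomized procedure. A clock that starts at TAVI therefore starts after the intervention under test has been delivered and most of its early risk has passed. A patient who dies of a PCI complication or during the wait has no time zero and cannot appear in the comparison. The article itself lists death, MI, stroke, access complications and renal insufficiency among the risks of PCI.

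The abstract names 30-day mortality as a secondary efficacy outcome, and the trial is meant to help decide whether the extra procedure can safely be avoided. An early mortality comparison that is blind to the period of that procedure cannot inform the question. The other 30-day events could be read on either clock, and each clock leaves out a different part of the test strategy.

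**Working it through.** **The plan's own figure.** The plan gives no figure on this point. Its power for the primary endpoint (at least 88.8%) reproduces and is not in dispute. With independent components, the control rate is 1 − 0.70 × 0.85 = 40.5% and the test rate is 1 − 0.80 × 0.85 = 32.0%. With 155 × 0.95 = 147.25 per arm (1:1 allocation assumed), SE = √[(0.405 × 0.595 + 0.32 × 0.68)/147.25] = 0.0558. Then (0.075 + 0.085)/0.0558 − 1.645 = 1.22, which gives 88.9%.

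**Step 1: calendar.** Let L be the days from randomization to PCI (L ≥ 0, not given). A test patient on schedule has TAVI on day L + 30 to L + 44.

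| L (assumed) | TAVI, day | 30 days post-TAVI, day | 12 months post-TAVI, day | Post-TAVI days accrued by day 30 |
|---|---|---|---|---|
| 0 | 30–44 | 60–74 | 395–409 | 0 |
| 14 | 44–58 | 74–88 | 409–423 | 0 |
| 28 | 58–72 | 88–102 | 423–437 | 0 |

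The last column is 0 for every L. In addition, 12 months post-TAVI falls after day 365, although event monitoring is described as running from randomization to 12 months.

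**Step 2: mortality on the stated TAVI clock.** Input: 20% 12-month test-arm mortality (Sample size determination). Assumption: constant hazard.
- 30-day interval: 1 − 0.8^(30/365) = 1.8%
- 44-day interval: 1 − 0.8^(44/365) = 2.7%

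In 155 test patients that is about 2.8 to 4.1 deaths left out. The figure is gross, because controls who die before TAVI are also left out. If controls had no wait, the control omission would be 0. With an assumed 30-day wait at the plan's 30% control mortality it would be 1 − 0.7^(30/365) = 2.9%. The net bias can therefore lie anywhere between these cases, and its sign is not fixed by the article.

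**Step 3: other 30-day events, both clocks.** This is for direction only. Assume the same early TAVI event risk of 10% in both arms. That number is borrowed from the registry in-hospital mortality in patients with coronary disease cited in the Background; it is not a MACCE rate. Assume a PCI-plus-wait risk of 2% (range 1% to 3%). Let s be the share of controls whose TAVI and early risk fall before day 30.

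| s | Test, day 30 from randomization | Control = s × 10% | Difference (range over 1% to 3%) |
|---|---|---|---|
| 1 | 2% | 10% | −8 points (−9 to −7) |
| 0.5 | 2% | 5% | −3 points (−4 to −2) |
| 0 | 2% | 0% | +2 points (+1 to +3) |

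On the TAVI clock both arms show 10%, although the test strategy's risk through 30 days post-TAVI is 1 − 0.98 × 0.90 = 11.8% (10.9% to 12.7%).

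**Step 4: does the attribution rule help?** It assigns events in the PCI-to-TAVI period to PCI, but does not say how they enter a 30-day rate. If they were added to the post-TAVI 30-day rate, the test arm would contribute 60 to 74 days from PCI against 30 days in control.

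**The case against.** **The origin can be left to the analysis plan.** For MACCE, MI, stroke and heart-failure hospitalization, an unstated origin alone would be no finding. But the mortality origin is stated, and it is the problem. For the other events, neither obvious choice gives a comparison of full strategies under the stated schedule.

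**PCI-period events are not lost.** This stands. Monitoring starts at randomization, PCI-related MI types are defined, bleeding, access-site and kidney outcomes carry no 30-day limit, and the primary endpoint counts deaths and rehospitalizations from randomization. A reader might infer that PCI complications vanish from the trial. They drop out only of rates counted from TAVI.

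**A day-30 comparison from randomization is valid by intention to treat.** This also stands. A reader might infer that 30-day outcomes cannot compare the arms at all. That is too strong: such a comparison is legitimate, but it sets PCI plus waiting against whatever controls have received by then.

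**The visits are probably post-TAVI already.** The echo and ECG sequence puts 1 month after a post-procedure assessment, and PCI tracings are listed separately as additional. It is therefore not supported to say that the 1-month echo and 30-day questionnaire are taken while test patients' valves are untreated. The visits need only a clarifying label.

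**A large excess of TAVI deaths in the control arm by day 30.** A reader might take Step 3 as a mortality bias of several points. Mortality is counted from TAVI in the article, so that reading does not apply to it. Control-arm timing is also not given, and at s = 0 the difference reverses.

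**The schedule is a recommendation.** The article says should, so the calendar describes patients treated on schedule, not every patient.

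**Conclusion.** The point holds for secondary mortality as a stated rule. Counting from TAVI conditions on a post-randomization event, leaves out test-arm deaths from PCI and the wait, and contradicts the intention-to-treat commitment. The illustrative size is 1.8% to 2.7% of test patients left out. This rests on the plan's 20% annual mortality and a constant hazard. That 20% includes deaths from TAVI itself, so the true hazard before TAVI could differ. The net between-arm bias depends on control-arm waiting time, which the article does not give.

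For 30-day MACCE, MI, stroke and heart-failure hospitalization, both candidate origins fail to compare the full strategies. The size and direction of the bias on the randomization clock depend on control-arm TAVI timing, so no single figure can be given. The primary endpoint, which runs from randomization, is unaffected. The clinical schedule is not challenged.

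**What to change.** 1. Use randomization as the origin for every between-arm comparison of mortality and events, at 12 months and at one early landmark.
2. Set the landmark after TAVI and its 30-day period are due in both arms. On schedule the test arm needs day L + 74. A 90-day landmark therefore suffices only if PCI occurs within 90 − 74 = 16 days of randomization. Check it against actual timing in both arms, without reference to outcomes by arm, before fixing it.
3. Report 30-day post-PCI and 30-day post-TAVI rates as descriptive procedural outcomes, with the number in each arm who did not reach TAVI.
4. State that the 30-day and 1-month questionnaire, echo and ECG are post-TAVI visits in both arms.

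**Cost.** Wording of the secondary endpoints and the analysis section. Events are already collected from randomization, so no new event collection is needed. The downside is that the early comparative time point is no longer the conventional 30 days, although 30-day figures remain available descriptively for comparison with other TAVI reports.
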